**Fig. 3 Fig3:**
[figure not shown]
Summary of the Bump2Baby and Me intervention components and frequency of each in the app

The intervention consists of six components as follows:
Synchronous mHealth coaching: Coaching sessions are conducted on a 1:1 basis between the mHealth coach and participants. There will be 2 synchronous sessions, the first at enrolment and the second between 4 and 8 weeks postpartum. These sessions will last 45–50 min with a follow-up summary video message of the goals discussed and, at the first session, the establishment of a behaviour change agreement. These sessions are mediated through a live-video feature in the mHealth coaching app. If the woman is diagnosed with GDM, there will be an opportunity for a third 15-min synchronous coaching session to review and adjust any lifestyle goals to align with the individual’s diabetes in the pregnancy management plan.Asynchronous mHealth coaching: This uses a combination of text and video messaging exchanges between the mHealth coach and participant and tailored to the woman’s needs. The pregnancy interactions will be once a week for the first 4 weeks. The mHealth coaching then becomes bi-weekly for 2 months and then monthly until birth. The postpartum interactions will be after the second synchronous coaching session. These will happen bi-weekly for 1 month, to support the woman to ease back into mHealth coaching contact after the birth. After that, it will be weekly for a month, then bi-weekly for a month prior to monthly check-ins with the mHealth coach. However, this will be arranged with the woman during the postpartum synchronous coaching session and will be adapted accordingly. From 6 to 12 months postpartum, asynchronous coaching will happen monthly.Automated push notifications: These will include messages prompting the individual to follow through on the goals they have set for themselves, reminders to register goal achievements, and motivational messages when they have accomplished their goals. Whilst these are standardised messages, their frequency of delivery will be tailored to match the individual’s goals. For example, if a woman sets a weekly goal to exercise, they will receive a weekly push reminder about this goal.Personalised educational content: Provided by the mHealth coach during the asynchronous coaching sessions, this content will cover topics within navigating the healthcare system and antenatal appointments, healthy eating for pregnancy and postpartum, physical activity, emotional well-being, breastfeeding, and best practice formula feeding. Each mHealth coach will continuously assess what content is relevant before sending it to the women.Additional support content: Participants will also receive automated push notifications referring to additional content available in the app. The content push notifications will be active once a week during the weeks that no asynchronous mHealth coaching occurs. These push notifications will connect participants with specially designed online resources providing tailored information such as recipes, tips for food and activity choices, breastfeeding resources, and links to relevant support agencies.Virtual social network: Participants will have access through the mHealth coaching app to a network with other women participating in the intervention arm of the study where messages can be sent. This will enable social engagement and support, as well as the capacity to connect physically for shared activities, self-organised in each study site.

### Control

The control group participants will be provided with standard written information for their site and links to approved country-specific national websites on the prevention of gestational diabetes, managing gestational weight gain, encouraging breastfeeding, postpartum weight loss, and diabetes prevention. They will also be provided with the details of the Bump2Baby website (www.bump2babyandme.org) which contains information in line with standard care for each site.

To improve retention throughout the study, both groups will receive electronic newsletters updating them on the progress of the study, and reminders to access the Bump2Baby website information, as they progress through their pregnancy and first year of motherhood. All study information will also be available on the website.

### Outcome measurements

The primary outcome is a reduction of 0.8 kg/m^2^ maternal BMI in the intervention group at 12 months postpartum.

The secondary outcomes will include the differences in the following measured during pregnancy and postpartum (Table 1):
Gestational weight gain and weight statusMaternal blood pressureMaternal physical activity and sleepMaternal psychological healthMaternal and infant dietMetabolic markers including blood glucose and blood lipidsGlycaemic status and GDM diagnosisBirth data including mode of delivery, birth weight, placental weight, and any complicationsNewborn and infant anthropometry (weight centiles, BMI *z*-scores)Breastfeeding (any and exclusivity) and durationInfant developmentInfant physical activity and sedentary time

**Table. 1 Tab1:** Domains and assessment questionnaires for secondary analyses in the Bump2Baby and Me Study

Domain	Measurement/questionnaire	Details	Time point measured	References

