**Maternal**				
**Diet**	Food4Me Food Frequency Questionnaire (FFQ)	Contains questions on the average consumption of 157 food items over the previous month. Food portion size is estimated using photographs. The questionnaire has been validated against standard food frequency questionnaires and 4-day weighed food diaries, in multiple countries including Ireland, Spain, and the UK. **Measurements units**: Continuous: nutrient values Categorical: meeting dietary guidelines **Analysis:** Compare mean/median and SD/IQR and meeting guidelines (yes/no)	- Pregnancy (12–24 weeks’ gestation) - Postpartum (12 months)^a^	[31]
** Physical activity**	1. Pregnancy Physical Activity Questionnaire (PPQA) 2. Smartphone app inbuilt activity tracker (intervention group only)	1. The PPQA was identified as the most psychometrically sound self-reported measure of physical activity in pregnancy. It is available in English and Spanish. 2. The smartphone inbuilt activity tracking capabilities of individuals phones will be used to record physical activity for the intervention group. This will be used to record the estimated step count for participants. **Measurement units:** Continuous: metabolic equivalent minutes (METs), Time spent in moderate/vigorous physical activity, steps per day. Categorical: Meeting physical activity recommendations **Analysis:** Compare mean/median and SD/IQR and meeting guidelines (yes/no)	- Pregnancy (12–24 weeks’ gestation) - Postpartum (12 months)^a^	[32, 33]

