**Breastfeeding**	1. Iowa Infant Feeding Attitudes Scale (IIFAS) 2. Adapted version of the Australian National Infant Feeding Survey 2010 and InFANT Extend Study	1. The IIFAS has been validated in English and Spanish, with good reliability. 2. Adapted questions will be used from the Australian National Infant Feeding Survey and InFANT Extend Study to assess levels of breastfeeding, feeding styles (including combinations of breast milk and formula), experience of pumping, timing and frequency of feeding, and age of weaning. **Measurement units:** Continuous: IIFA score (17–85) Categorical: IIFAS scores will be categorised into groups: (1) positive to breastfeeding, (2) neutral, and (3) positive to formula feeding. Groups will be created based on previous breastfeeding experience, breastfeeding intentions, and meeting breastfeeding and infant feeding recommendations. **Analysis:** Compare the mean/median and SD/IQR and categories	- Pregnancy (12–24 weeks’ gestation) - Postpartum (3, 6, 9, 12^a^ months)	[34–37]
**Health status**	EuroQol-5 Dimension (EQ 5-D-L)	The EQ 5-D-L is a standardised instrument for measuring generic health status and has been extensively validated in over 200 countries. **Measurement units:** Continuous: self-rated EQ visual analogue scale (1–100), score 1–5 for five dimensions: mobility, self-care, usual activities, pain/discomfort, and anxiety/depression (score 1–5) Categorical: high/low across the five dimensions **Analysis:** Compare scores in categories, mean/median, and SD/IQR for visual analogue scale	- Pregnancy (12–24 weeks’ gestation) - Postpartum (12 months)^a^	[38, 39]
**Psychological health**	Edinburgh Postnatal Depression Scale (EPDS)	The EDPS is a questionnaire originally developed to assist in identifying possible symptoms of depression in the postpartum period. It also has adequate sensitivity and specificity to identify depressive symptoms in the antenatal period and is useful in identifying symptoms of anxiety. The EDPS has been extensively validated in multiple languages including Spanish, with good sensitivity, reliability and established validity against diagnostic interviews. **Measurement units:** Continuous: score (1–25) Categories: at-risk of depression (< 13, yes/no) **Analysis:** Compare the mean/median and SD/IQR and categories	- Pregnancy (12–24 weeks’ gestation) - Postpartum (3, 6, 9, 12^a^ months)	[40–42]

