**Sleep quality**	Pittsburgh Sleep Quality Index (PSQI)	The PSQI is a self-report questionnaire that assesses sleep quality over a 1-month time interval. The PSQI is one of the most widely used sleep questionnaires and has been translated and validated into multiple languages, including Spanish, and amongst antenatal and postpartum populations. **Measurement units:** Continuous: total score (0–21), 7 subscores (0–3) Categories: poor sleep quality (> 5, yes/no) **Analysis:** Compare the mean/median and SD/IQR and categories	- Pregnancy (12–24 weeks’ gestation) - Postpartum (3, 6, 9, 12^a^ months)	[43–45]
**Health literacy**	Health Literacy Questionnaire (HLQ) and electronic Health Literacy Questionnaire (eHLQ)	The HLQ and eHLQ are a series of independent scales that assess functional health literacy and the fuller constructs of health literacy. The HLQ has extensive cross-cultural validity and has translations available in Spanish. The eHLQ is well-defined, validated, and reliable and was designed to evaluate interactions with digital health services. **Measurement units:** Continuous: 9 subscales scores (1–5) Categories: adequate/inadequate health literacy **Analysis:** Compare the mean/median and SD/IQR and categories	- Pregnancy (12–24 weeks’ gestation) - Postpartum (12 months)^a^	[46, 47]
**Willpower**	6 Implicit Theories of Willpower – Resisting Temptation (ITW-RT)	The ITW-RT scale has been shown to have good psychometric properties, including predictive and concurrent validity. **Measurement units:** Continuous: total score (1–30) Categories: non-limited theory of willpower (score 0–17), limited theory of willpower (18–30) **Analysis:** Compare the mean/median and SD/IQR and categories	- Pregnancy (12–24 weeks’ gestation) - Postpartum (12 months)^a^	[48–50]

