### Baseline assessments

Participants will attend the first study visit after recruitment in line with routine antenatal care. A researcher will facilitate participants in the intervention group with onboarding, including downloading the mHealth coaching app, account creation, and scheduling the initial coaching session. For participants in the control group, the research clinician will provide the women with a written leaflet with details of the approved website and show the woman how to access the health information on the Bump2Baby website. Demographic characteristics will be collected via questionnaire and will include maternal age, ethnicity, gravidity, parity, relationship status, educational attainment, employment status (of the participant and relevant partner), housing status, childcare responsibilities, and prior medical history.

Anthropometric measurements of maternal height (cm) and weight (kg) will be extracted from medical records, and all participants will also be provided with a set of digital scales (Smart Body Fat Scale, RENPHO©) for the duration of the study. Participants will be provided with a manual on how to use the scales appropriately and will be asked to weigh themselves approximately once a week. The scales will connect via Bluetooth, with an app on the participant’s phone, which facilitates automatic recording of this data when the individual is connected to a wireless network. Body mass index (BMI, kg/m^2^) will be calculated from these measurements. Blood pressure will also be measured using a calibrated blood pressure monitor at the baseline visit.

Participants will be asked to complete the online questionnaires, detailed in Table 1, within 1 week of the baseline visit before the first health coaching session for the intervention group.

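### The single pregnancy reading of maternal diet, activity, sleep and psychological health is a pre-coaching baseline; the outcome list and the model should treat it as one

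*Protocol article*

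**What the plan says.** Outcome measurements opens the list of secondary outcomes with "The secondary outcomes will include the differences in the following measured during pregnancy and postpartum (Table 1". The list has twelve items, among them maternal physical activity and sleep, psychological health, and diet.

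Table 1 gives the timing:
- **Diet and physical activity:** "Pregnancy (12–24 weeks’ gestation) - Postpartum (12 months".
- **Psychological health (EPDS) and sleep (PSQI):** "Pregnancy (12–24 weeks’ gestation) - Postpartum (3, 6, 9, 12^a^ months".

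The table footnote says that, where a measure is taken more than once, the time marked with the superscript is the one of main interest. For all four domains that mark is on 12 months postpartum.

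Baseline assessments asks for these questionnaires "within 1 week of the baseline visit before the first health coaching session for the intervention group". Antenatal assessments then lists weight, OGTT results and scan data, and repeats no questionnaire. Table 1 has one further source of activity data, the "Smartphone app inbuilt activity tracker (intervention group only".

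Statistical analyses evaluates secondary outcomes by repeated-measures ANOVA or mixed models. Each participant contributes every time-specific measurement, and site is the only covariate expected.

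**The concern.** The lead-in can be read as promising an arm comparison during pregnancy as well as after it. For these four domains the schedule cannot supply one, because the only pregnancy value is taken before coaching can have acted. An arm difference at that reading would reflect chance imbalance. Since it is taken after randomisation, it might also reflect a reaction to allocation.

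Two things are at stake. The first is interpretation: the Background argues for lifestyle change starting in pregnancy and the abstract lists improvements in diet, activity and sleep, so a reader may look for an antenatal result that the data cannot give. The second is analysis: a pre-coaching value used as one more response is not adjusted for, and its place in the model leaves the arm effect open to being read over all times instead of the postpartum times.

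**Working it through.** The article states no figure to reproduce here. The check sets the schedule, the timing rule and the model side by side.

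**1. Comparative readings between the start of coaching and birth**
- Diet, physical activity, EPDS and PSQI: one pregnancy reading each (Table 1), placed before the first coaching session (Baseline assessments). Post-coaching antenatal readings: 0.
- Step tracker: intervention arm only, so it allows no arm comparison.
- Antenatal assessments: no questionnaire.

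**2. Length of the gap**
Assume birth at 37–40 weeks, and count 3 months as 13 weeks and 12 months as 52 weeks. Baseline is at 12–24 weeks (Table 1).
- Baseline to birth: 37 − 24 = 13 weeks to 40 − 12 = 28 weeks.
- Baseline to the next EPDS and PSQI reading (3 months postpartum): 13 + 13 = 26 to 28 + 13 = 41 weeks.
- Baseline to the next diet and activity reading (12 months postpartum): 13 + 52 = 65 to 28 + 52 = 80 weeks.

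**3. Can the later readings reach back into pregnancy?**
The diet questionnaire covers "average consumption of 157 food items over the previous month", and the PSQI "assesses sleep quality over a 1-month time interval". At 12 and 3 months postpartum respectively, a one-month window does not reach pregnancy. Table 1 gives no recall period for the EPDS or the activity questionnaire, and does not present their postpartum readings as covering pregnancy.

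**4. Effect of the model as written**
Let d be the postpartum arm difference, with an expected difference of 0 at baseline.
- If the reported quantity were an arm main effect averaged equally over k times including baseline, it would be (k − 1)/k × d, with d constant postpartum.
- Diet and activity, k = 2: (2 − 1)/2 = 1/2 of d.
- EPDS and PSQI, k = 5: (5 − 1)/5 = 4/5 of d.
- If the reported quantity is the arm difference at a postpartum time, or the arm-by-time contrast, there is no dilution.

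**5. Why a covariate is better than a response**
Let ρ be the correlation between the baseline and postpartum readings, with equal variances and complete data. Relative to the variance of the unadjusted postpartum difference:
- unadjusted postpartum difference: 1;
- difference in change from baseline: 2(1 − ρ);
- baseline as covariate: 1 − ρ² = (1 − ρ)(1 + ρ).

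Since 1 + ρ ≤ 2 and ρ² ≥ 0, the last is no larger than either of the others. The article gives no ρ, so the size of the gain cannot be stated.

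**The case against.** The strongest reply is that the protocol already treats the reading as baseline. The questionnaires are described under Baseline assessments, the Table 1 footnote names 12 months postpartum as the time of interest, and Statistical analyses speaks of differences between baseline and 12 months, though only within arms. The lead-in covers twelve items and cannot apply in full to each: infant development is not measured in pregnancy, and gestational weight gain is not a postpartum measure. Keeping baseline in the response vector is also a standard choice when the contrast is at a postpartum time, and the contrast may be fixed in the analysis plan, which is not shown.

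Most of this stands. A reader might infer that the protocol promises an antenatal effect on these domains, that its secondary estimates will be diluted, or that the early reading will be tested and reported as an antenatal effect. The documents support none of these. The first over-reads a general lead-in. The second needs an arm main effect averaged over all times including baseline, which the article neither specifies nor rules out. The third needs a test that no section plans; the baseline tests that are planned only describe the groups.

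What the reply does not remove is the article's own statement that site is the only covariate expected while all time-specific measurements enter the model. That is stated text, not a gap left to another document, and it leaves the pre-coaching value unused as an adjustment.

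**Conclusion.** The point holds as a modest improvement to wording and model. Between the first coaching session and birth there are no comparative readings of maternal diet, physical activity, sleep or psychological health, so no between-arm antenatal effect on them can be estimated. The unmeasured period is about 13 to 28 weeks, on the assumption of birth at 37–40 weeks. The planned postpartum comparison is sound in design, with 12 months already marked as the main time.

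The factors of 1/2 and 4/5 are conditional and should not be read as a bias in the plan. The point does not extend to gestational weight gain, GDM diagnosis or birth data, which are recorded after coaching starts.

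The conclusion rests on the questionnaires being completed before coaching. Baseline assessments says so, while Intervention places the first synchronous session at enrolment. On either account the reading falls at the start of coaching, so the conclusion does not change, but the two sections must be reconciled.

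**What to change.** 1. **Outcome measurements:** state maternal diet, physical activity, sleep and psychological health as postpartum outcomes, with 12 months as the main time point and 3, 6 and 9 months also for sleep and EPDS. This brings the list into line with the Table 1 footnote.
2. **Statistical analyses:** enter the 12–24 week value as a baseline covariate alongside site, or keep it in the response vector with the arm means constrained to be equal at baseline. Report the arm difference at the postpartum times.
3. **Reporting:** make no antenatal behaviour-change claim from the 12–24 week reading. Limit antenatal claims to outcomes recorded after coaching starts.
4. **Timing:** reconcile Intervention and Baseline assessments on when the first coaching session falls relative to the questionnaires, and confirm from completion dates that each baseline questionnaire preceded it.

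The cost is wording and model specification, with no new data. There are two small downsides. The questionnaire is completed after randomisation, so its use as a baseline depends on the check in item 4 and on allocation itself not having changed the answers. Women without a baseline questionnaire would drop out of a simple covariate model; the multiple imputation already planned, or the constrained-baseline model, keeps them in.

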**Maternal**				
**Diet**	Food4Me Food Frequency Questionnaire (FFQ)	Contains questions on the average consumption of 157 food items over the previous month. Food portion size is estimated using photographs. The questionnaire has been validated against standard food frequency questionnaires and 4-day weighed food diaries, in multiple countries including Ireland, Spain, and the UK. **Measurements units**: Continuous: nutrient values Categorical: meeting dietary guidelines **Analysis:** Compare mean/median and SD/IQR and meeting guidelines (yes/no)	- Pregnancy (12–24 weeks’ gestation) - Postpartum (12 months)^a^	[31]
** Physical activity**	1. Pregnancy Physical Activity Questionnaire (PPQA) 2. Smartphone app inbuilt activity tracker (intervention group only)	1. The PPQA was identified as the most psychometrically sound self-reported measure of physical activity in pregnancy. It is available in English and Spanish. 2. The smartphone inbuilt activity tracking capabilities of individuals phones will be used to record physical activity for the intervention group. This will be used to record the estimated step count for participants. **Measurement units:** Continuous: metabolic equivalent minutes (METs), Time spent in moderate/vigorous physical activity, steps per day. Categorical: Meeting physical activity recommendations **Analysis:** Compare mean/median and SD/IQR and meeting guidelines (yes/no)	- Pregnancy (12–24 weeks’ gestation) - Postpartum (12 months)^a^	[32, 33]
**Breastfeeding**	1. Iowa Infant Feeding Attitudes Scale (IIFAS) 2. Adapted version of the Australian National Infant Feeding Survey 2010 and InFANT Extend Study	1. The IIFAS has been validated in English and Spanish, with good reliability. 2. Adapted questions will be used from the Australian National Infant Feeding Survey and InFANT Extend Study to assess levels of breastfeeding, feeding styles (including combinations of breast milk and formula), experience of pumping, timing and frequency of feeding, and age of weaning. **Measurement units:** Continuous: IIFA score (17–85) Categorical: IIFAS scores will be categorised into groups: (1) positive to breastfeeding, (2) neutral, and (3) positive to formula feeding. Groups will be created based on previous breastfeeding experience, breastfeeding intentions, and meeting breastfeeding and infant feeding recommendations. **Analysis:** Compare the mean/median and SD/IQR and categories	- Pregnancy (12–24 weeks’ gestation) - Postpartum (3, 6, 9, 12^a^ months)	[34–37]
**Health status**	EuroQol-5 Dimension (EQ 5-D-L)	The EQ 5-D-L is a standardised instrument for measuring generic health status and has been extensively validated in over 200 countries. **Measurement units:** Continuous: self-rated EQ visual analogue scale (1–100), score 1–5 for five dimensions: mobility, self-care, usual activities, pain/discomfort, and anxiety/depression (score 1–5) Categorical: high/low across the five dimensions **Analysis:** Compare scores in categories, mean/median, and SD/IQR for visual analogue scale	- Pregnancy (12–24 weeks’ gestation) - Postpartum (12 months)^a^	[38, 39]
**Psychological health**	Edinburgh Postnatal Depression Scale (EPDS)	The EDPS is a questionnaire originally developed to assist in identifying possible symptoms of depression in the postpartum period. It also has adequate sensitivity and specificity to identify depressive symptoms in the antenatal period and is useful in identifying symptoms of anxiety. The EDPS has been extensively validated in multiple languages including Spanish, with good sensitivity, reliability and established validity against diagnostic interviews. **Measurement units:** Continuous: score (1–25) Categories: at-risk of depression (< 13, yes/no) **Analysis:** Compare the mean/median and SD/IQR and categories	- Pregnancy (12–24 weeks’ gestation) - Postpartum (3, 6, 9, 12^a^ months)	[40–42]
**Sleep quality**	Pittsburgh Sleep Quality Index (PSQI)	The PSQI is a self-report questionnaire that assesses sleep quality over a 1-month time interval. The PSQI is one of the most widely used sleep questionnaires and has been translated and validated into multiple languages, including Spanish, and amongst antenatal and postpartum populations. **Measurement units:** Continuous: total score (0–21), 7 subscores (0–3) Categories: poor sleep quality (> 5, yes/no) **Analysis:** Compare the mean/median and SD/IQR and categories	- Pregnancy (12–24 weeks’ gestation) - Postpartum (3, 6, 9, 12^a^ months)	[43–45]
**Health literacy**	Health Literacy Questionnaire (HLQ) and electronic Health Literacy Questionnaire (eHLQ)	The HLQ and eHLQ are a series of independent scales that assess functional health literacy and the fuller constructs of health literacy. The HLQ has extensive cross-cultural validity and has translations available in Spanish. The eHLQ is well-defined, validated, and reliable and was designed to evaluate interactions with digital health services. **Measurement units:** Continuous: 9 subscales scores (1–5) Categories: adequate/inadequate health literacy **Analysis:** Compare the mean/median and SD/IQR and categories	- Pregnancy (12–24 weeks’ gestation) - Postpartum (12 months)^a^	[46, 47]
**Willpower**	6 Implicit Theories of Willpower – Resisting Temptation (ITW-RT)	The ITW-RT scale has been shown to have good psychometric properties, including predictive and concurrent validity. **Measurement units:** Continuous: total score (1–30) Categories: non-limited theory of willpower (score 0–17), limited theory of willpower (18–30) **Analysis:** Compare the mean/median and SD/IQR and categories	- Pregnancy (12–24 weeks’ gestation) - Postpartum (12 months)^a^	[48–50]

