Baseline characteristics will be compared between the intervention and control groups using the *χ*^2^ tests, the independent *t*-tests, and/or the Wilcoxon rank-sum test, as appropriate. Primary and secondary outcomes will be evaluated using repeated-measures analysis of variance (ANOVA) or mixed model analyses. Two-sided tests will be used, with a level of *P* < 0.05 determining statistical significance. Comparisons of the assessment times (the baseline and 12 months postpartum differences) within each treatment group (control or intervention) will be based on *t*-tests that utilise the standard errors of the differences that are computed as part of the repeated-measures analysis. Covariates included in the model will be kept to a minimum—site is the only covariate expected. The impact of loss to follow-up will be minimised by using a marginal model, which is not subject to list-wise deletion: each participant will contribute all time-specific measurements made to the model. Missing data will be reported for each outcome and handled by applying multiple imputation methods [60]. Subgroup analyses will be carried out to investigate the site differences based on the substantial demographic and operative differences in the four clinical sites. There are no interim analyses planned. Analyses will be conducted using the IBM SPSS software (version 26.0 or later; IBM), STATA version 12 or later (Stata Corp., College Station, TX, USA), or SAS software (SAS Institute Inc., Cary, NC, USA), as appropriate for analysis type. Data analysts will be blinded to group assignments.

A statistical analysis plan and data management plan have been prepared for the project which outlines plans for data entry, coding, confidentiality, security, and analysis in line with best practice (Additional file 2). Each clinical site is incorporated in this data management plan and provided the details to their relevant ethics committee. The project has an independent data manager who oversees the data monitoring and analyses and reports back to the RCT Working Group. There is no formal data monitoring committee; however, the external advisory board receives reports from the data manager.

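### Table 1 appears to reverse the EPDS at-risk inequality (< 13): coded as written, the categorical depression comparison between arms would change sign

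*Protocol article*

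**What the plan says.** Maternal psychological health is one of the secondary outcomes listed under Outcome measurements. Table 1 (Maternal, Psychological health) assigns it to the EPDS, collected in pregnancy and at 3, 6, 9 and 12 months postpartum. The table's footnote marks the 12-month value as the one of main interest.

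The row describes the EPDS as a "questionnaire originally developed to assist in identifying possible symptoms of depression in the postpartum period" and adds that it can also pick up depressive symptoms before birth. It gives two forms of the outcome:

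- a continuous form, "Continuous: score (1–25";
- a categorical form, "Categories: at-risk of depression (< 13, yes/no".

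The stated analysis covers both: "Compare the mean/median and SD/IQR and categories".

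The next row, for the Pittsburgh Sleep Quality Index (PSQI), puts its adverse category above a cut-off: "Categories: poor sleep quality (> 5, yes/no".

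**The concern.** A score built to detect depressive symptoms is naturally read as rising with symptoms. On that reading, women at risk are those with high scores. The printed rule assigns the label to scores below 13, so on the stated range a woman scoring 1 is at risk and a woman scoring 25 is not.

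This is not detail that the article leaves to the SAP. It is a derivation rule that the article states, and states in what looks like the wrong direction. If an analyst follows it, the arm with fewer symptomatic women will show the higher at-risk rate, and a benefit will read as harm or harm as benefit. If the analyst instead codes the sensible direction without a recorded correction, the reported outcome will differ from the published definition and may look like an undeclared change.

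**Working it through.** The documents give no figure to reproduce: no EPDS rate, effect or power appears in them. The check has two parts.

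**1. What the printed rule does on the stated range.** With whole-number scores from 1 to 25:

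- below 13 (printed rule): 12 values, 1 to 12, are at risk;
- 13 or above: 13 values, 13 to 25, are not at risk under the printed rule.

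The printed at-risk group is therefore exactly the complement of the group scoring 13 or more.

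**2. What that does to the comparison of arms.** Let p_I and p_C be the proportions scoring 13 or more in the intervention and control arms. The printed rule analyses 1 − p_I and 1 − p_C. Then:

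- risk difference: (1 − p_I) − (1 − p_C) = −(p_I − p_C), the same size with opposite sign;
- odds ratio: the reciprocal of the odds ratio for scoring 13 or more;
- risk ratio: (1 − p_I)/(1 − p_C), which crosses 1 but is not the reciprocal;
- two-sided test: the variance terms p(1 − p) do not change when p is replaced by 1 − p, so the p-value and power are unchanged.

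The inputs from the article are two-sided testing at the 5% level (Statistical analyses), and 400 women per arm with 70% retention (Sample size), which gives 400 × 0.70 = 280 per arm. The proportions below are assumptions chosen to show a range.

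| Scoring ≥ 13, control vs intervention | Risk difference (≥ 13 → < 13), points | Odds ratio (≥ 13 → < 13) | Risk ratio (≥ 13 → < 13) | Reported at risk under < 13, control vs intervention | Power, 280 per arm (≥ 13 / < 13) |
|---|---|---|---|---|---|
| 10% vs 5% | −5 → +5 | 0.47 → 2.11 | 0.50 → 1.06 | 90% vs 95% | 0.613 / 0.613 |
| 15% vs 10% | −5 → +5 | 0.63 → 1.59 | 0.67 → 1.06 | 85% vs 90% | 0.432 / 0.432 |
| 20% vs 15% | −5 → +5 | 0.71 → 1.42 | 0.75 → 1.06 | 80% vs 85% | 0.343 / 0.343 |
| 25% vs 15% | −10 → +10 | 0.53 → 1.89 | 0.60 → 1.13 | 75% vs 85% | 0.843 / 0.843 |

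Worked line, 15% vs 10%: the odds ratio for ≥ 13 is (0.10/0.90)/(0.15/0.85) = 0.63. Under the printed rule it is (0.90/0.10)/(0.85/0.15) = 1.59 = 1/0.63.

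**Boundary.** The exact mirror image holds against a rule of 13 or above. If above 13 was meant, a woman scoring exactly 13 is not at risk under either rule. With r the proportion above 13 and q the proportion at exactly 13, the printed rule gives 1 − r − q. The risk difference then becomes −(r_I − r_C) − (q_I − q_C). The direction still reverses unless a difference at exactly 13 offsets it, but the size need not match.

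**The case against.** The strongest reply is that this is probably a typographical slip that would do no harm. The SAP (Additional file 2) and the derivation code are not shown and may carry the right sign. On the assumed rates, the printed rule would report 75% to 95% of women as at risk of depression, which an analyst would be likely to notice. The raw scores are kept, so the category can be re-derived at any time. The article attaches no eligibility, referral or stopping rule to the cut-off. It concerns one dichotomised form of one instrument, within one of twelve listed secondary domains. All of this stands, and it limits the consequence. It does not make the printed definition right.

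A second reply is that the row never states which end of the scale is worse. That is true: the direction is inferred from the scale's name and its described purpose. The PSQI row supports the reading only by analogy, as a different instrument. The inference is still the only natural one.

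Three stronger readings are tempting but unsupported:

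- **That the trial's EPDS result will be reversed.** This happens only if the rule is programmed as printed.
- **That every woman would be misclassified.** This needs the intended rule to be exactly 13 or above. The article does not show whether the slip was for > or ≥, and under > 13 a score of 13 is classed the same way by both rules.
- **That the printed 1–25 range is also wrong.** Nothing in the article contradicts it.

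Nor does a reversed sign give a reason to rank the continuous score above the category. The row already plans both comparisons.

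**Conclusion.** The point holds as a definite but narrow error: a published outcome threshold that appears to point the wrong way, with no correction elsewhere in the article. If coded as written, it reverses the sign of the risk difference and inverts the odds ratio for the categorical EPDS comparison. The p-value and power do not change, so a reversed result would carry the same apparent certainty as a correct one. With assumed rates of 10% to 25% of controls scoring 13 or more, 75% to 90% of controls would be labelled at risk.

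This rests on two assumptions: that higher EPDS scores mean more symptoms, and, for the exact mirror image, that a score of 13 belongs to the at-risk group. The rates are illustrative. The continuous EPDS comparison and the primary BMI outcome are untouched.

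**What to change.** Before analysis:

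1. Reverse the inequality in Table 1 so that the at-risk category is the upper end of the EPDS.
2. Confirm from the instrument's scoring instructions whether a score of exactly 13 counts as at risk, and write the rule with > or ≥ accordingly.
3. Check that the SAP and the derivation code use the same direction and boundary. Amend them only if they repeat the slip.
4. Record the correction with its date, so that the reported category is not taken for an undeclared change of outcome.

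The cost is one line in Table 1 and a short check of two other items. Sample size, data collection and trial conduct are unaffected.
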